### Statistical methods

The Shapiro–Wilk test will be used to test for normality of the data while variance homogeneity and sphericity will be assessed with the Levene and Mauchly tests, respectively. To assess changes over time in the assessed outcomes, a repeated-measures ANOVA with Bonferroni correction will be used to assess the interaction between group (control group vs. WBV) and time (baseline vs. 2nd vs. 3rd vs. 4th assessments). In the absence of a normal distribution, data will be analyzed with the Wilcoxon test for within-group comparisons and the Mann–Whitney test for between-group comparisons using Bonferroni’s correction. To test for associations between variables, both correlations and linear regressions will be performed. The significance level will be set at 5%. Per-protocol and intention-to-treat analyses will be performed in order to account for the possible dropouts during the study. In the per-protocol analysis, we will include only the participants who attend at least 70% of the sessions and undergo the baseline and post-intervention outcome assessments. For the intention-to-treat analysis, we will consider all the participants who will undergo the baseline assessments and subsequently participate in at least one additional assessment following their group assignment will be considered.

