### Participants

#### Sample size

The sample size for the present study was calculated using G*POWER 3.1. The F-test family, repeated measures, within-between interaction for two groups and four measurements was selected, assuming a correlation among the repeated measurements of 0.5. A total of 12 participants per group were required to achieve a power of 80% with a significance level of 5% under the assumption that we would find small-medium effect sizes (partial eta square of 0.06). This would entail a total of 24 participants. In the event of a 15% attrition rate during the experiment, it would be necessary to recruit an additional 3.6 participants. Consequently, the final study sample would be of 28 participants (14 per group).

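### The fallback for non-normal outcomes is not specified as a test of the group-by-time interaction the trial is powered on, so a normality pre-test decides which question an outcome answers

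*Protocol article*

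**What the plan says.** Statistical methods states that "The Shapiro–Wilk test will be used to test for normality of the data". For the main analysis, "a repeated-measures ANOVA with Bonferroni correction will be used to assess the interaction between group (control group vs. WBV) and time", with four assessments. If normality is not met, "data will be analyzed with the Wilcoxon test for within-group comparisons and the Mann–Whitney test for between-group comparisons", again with a Bonferroni correction. The section does not say whether Shapiro–Wilk is applied to each arm at each visit, to the arms pooled, or to residuals. It does not say whether one rejection is enough to switch, or whether Mann–Whitney is applied to visit values or to changes.

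The Sample size section rests on the interaction alone: "The F-test family, repeated measures, within-between interaction for two groups and four measurements was selected", "assuming a correlation among the repeated measurements of 0.5", a partial eta-squared of 0.06, 5% significance and 80% power. This gives 12 per group, raised to 14 for attrition.

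Outcome variables lists perceived quality of life among four primary outcomes. The section on the quality-of-life questionnaires names the EQ-5D-5L with its 0 to 100 scale, and the SF-36.

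**The concern.** The interaction asks whether change over time differs between arms. The fallback has two parts, and neither is specified as an answer to that question. A Wilcoxon test within an arm compares visits and involves no other arm. A Mann–Whitney test on values at one visit compares levels at that visit and does not use each person's starting point. Two primary outcomes could therefore be judged on different hypotheses, with the choice made by a pre-test on 14 people per arm under a rule the protocol leaves open. The power claimed in Sample size does not carry over to an outcome that is switched.

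**Working it through.** **Inputs.** From Sample size: 2 groups, 4 measurements, ρ = 0.5, partial eta-squared 0.06, α = 0.05, 12 per group analysed and 14 recruited. Assumed, because the protocol does not state them: equal correlation between all visits, normal data, no dropout, a 5% level for Shapiro–Wilk, and two-sided rank tests.

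**1. The plan's own figure.** f² = 0.06/0.94 = 0.0638, so f = 0.2526. The noncentrality is λ = f²·N·m/(1−ρ) = 0.0638 × 24 × 4/0.5 = 12.26, with 3 and (24−2) × 3 = 66 degrees of freedom. Power is 82.5% at N = 24 and 78.4% at N = 22, so 24 is the smallest balanced total that reaches 80%. The stated size reproduces.

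**2. The gate, on truly normal data.** With q independent tests at 5%, P(at least one rejection) = 1 − 0.95^q.

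| Unit tested, any rejection switches | q | Formula | Simulated, ρ = 0.5 (12 / 14 per arm) | Simulated, ρ = 0.95 (12 / 14 per arm) |
|---|---|---|---|---|
| One test per outcome | 1 | 5.0% | not run | not run |
| Arms pooled at each visit | 4 | 18.5% | 18.9% / 17.8% | 11.2% / 11.7% |
| Each arm at each visit | 8 | 33.7% | 34.0% / 31.6% | 22.0% / 22.3% |

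Each simulation used 3,000 runs. The range is therefore 5% to about 34%.

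**3. What each test addresses.** Write μ(g,t) for the mean in arm g at visit t.

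- Interaction: is μ(WBV,t) − μ(control,t) the same at every visit?
- Mann–Whitney on visit values: do the arms differ at visit t?
- Mann–Whitney on change from T1: does change to visit t differ between arms? This is one piece of the interaction.
- Wilcoxon within an arm: does that arm change between two visits?

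**4. Rejection rates.** 6,000 runs per row, 12 per arm, ρ = 0.5. Mann–Whitney on values uses 0.05/4 over four visits. Mann–Whitney on change uses 0.05/3 over three changes.

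| True state | Interaction F | Mann–Whitney, values | Mann–Whitney, change |
|---|---|---|---|
| No effect of time or arm | 4.6% | 3.6% | 3.5% |
| Same time trend in both arms | 4.8% | 3.7% | 3.5% |
| Arms 0.8 SD apart at every visit | 4.8% | 48.6% | 4.0% |
| Planned f, crossing pattern | 82.4% | 25.1% | 60.7% |
| Planned f, arms equal at T1 and T2, apart at T3 and T4 | 82.6% | 54.8% | 60.4% |

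In the crossing row the arms differ by 2f = 0.51 SD at each visit, with the sign reversing after T2. In the last row they differ by 4f = 1.01 SD at T3 and T4. A repeat of the last row gave 84%, 54% and 61%.

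The third row shows only that the two tests ask different questions: a constant gap is no interaction. That row and the crossing row have arms that differ at T1, which randomisation excludes in expectation. The last row is closest to this trial, because 16 weeks of training fits between T2 (about 7 weeks after surgery) and T3 (about 24 weeks).

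**The case against.** **The article may leave the detail to a fuller plan.** The choice between values and changes, or between data and residuals, could be settled elsewhere. That is fair for those details. But the switch away from the interaction is a stated rule, and the tests it names include none for the interaction.

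**Mann–Whitney may be intended on change scores.** The text permits this, and such a test addresses a visit-specific part of the interaction (4.0% rejection under a constant gap). One therefore cannot say that the fallback fails to test the question, only that it is not specified to do so. Even on change, power is about 60%.

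**A reader might infer that a third of normal outcomes will be switched.** That needs all eight arm-by-visit cells to be tested, with any single rejection decisive. The protocol states no such rule, and other readings give as little as 5%.

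**A reader might infer inflated false positives.** With no arm difference, Mann–Whitney on visit values rejected in 3.6–3.7% of runs over four visits. It is a valid comparison of randomised arms.

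**A reader might infer that arms will be compared by significance in one arm and not the other.** With the same 0.8 SD fall by T3 in both arms, the unadjusted T1–T3 Wilcoxon test was significant in only one arm in 43.3% of runs, so that reading would be unsafe. But the protocol assigns between-group comparisons to Mann–Whitney and does not propose it. Within-arm tests also serve the first aim in Objectives, which is to describe the effect of the surgery.

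**Conclusion.** The point holds in limited form. The fallback is not specified as a test of the hypothesis that the trial is powered on, and an incompletely defined pre-test decides when it applies. For truly normal outcomes, misrouting ranges from 5% to about 34%. At the planned effect, power drops from about 82–84% to 25–55% on visit values (about 55% for the pattern closest to this trial) or about 60% on change.

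These figures assume normal data, equal correlations of 0.5, complete data on 12 per arm, and Bonferroni over visits. They describe normal outcomes sent to the fallback by mistake. For genuinely skewed outcomes the power comparison was not computed and could differ, but the change of question remains. Part of the loss comes from splitting one test into several corrected ones rather than from using ranks.

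How often the quality-of-life scores would fail the gate cannot be computed from the protocol. That they may well do so is a judgement from their bounded form. The defect is lost power and a changed question, and it should be corrected before analysis.

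**What to change.** - Drop the normality pre-test as a switch. Keep one between-arm analysis of change for every outcome: the planned group-by-time model or a baseline-adjusted equivalent.
- Check model residuals. Where they are clearly non-normal, use a transform, or a bootstrap or permutation p-value and confidence interval for the same contrast. Alternatively, use a rank-based test that takes baseline into account: rank ANCOVA, or at least Mann–Whitney on change.
- Keep the within-arm Wilcoxon tests only as a description of change after surgery, and state that they will not be used to compare arms.

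The cost is revised wording in Statistical methods and a few lines of code. Data collection and sample size do not change.

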### Intervention

#### Randomization, allocation, and blinding

In order to ensure fairness, individuals who meet the eligibility criteria will be randomly assigned (1:1) to either a WBV group or a CG through the webpage https://www.sealedenvelope.com, taking sex into account (1:1). At the second visit, both groups will be provided with a brochure outlining the World Health Organization’s physical activity recommendations, as well as an ad hoc nutritional information sheet. A nurse will be responsible for recruiting all participants and will then direct them to the researchers, who will inform the participants of their group allocation, in accordance with the randomized order. Both groups will receive standard care, but the intervention group will also engage in an exercise intervention as outlined below. Given that the intervention will comprise WBV and that researchers will be involved in it, only the nurse and the statistician performing the statistics will be blinded. There is no foreseeable reason for the statistician to be unblinded to participant allocation.

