##### Training frequency, intensity, and duration

Those allocated to the WBV group will attend three weekly supervised sessions for 16 weeks, with a total of 47 sessions completed (during the first week, only two sessions are performed). Participants will be permitted to select the time of day and day of the week for each session, provided that a minimum of 24 h elapsed between each session and that the training is not performed on three consecutive days.

The duration of the sessions will range from 28 to 46 min, with the intensity increasing weekly through an increase in the number of repetitions, time of vibration, or reduction in rest times as illustrated in Table 1.

In the WBV, all participants will receive the same stimulus, resulting in varying internal loads for each individual. Nevertheless, for the warm-up and the elastic band training, the resistances will be adjusted as previously explained in order to achieve a similar internal load for all participants.

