### Cost-effectiveness analysis

The economic analysis will be conducted from the perspective of the healthcare system with the objective of estimating the approximate cost of implementing this exercise program for this population. This analysis will include healthcare utilization and intervention costs. The health system cost will be recorded, including the visits of physicians and nurses in primary care, specialist physicians, physiotherapists, social workers, occupational therapists, and dietitian services; medication use; emergency rooms; hospital days; diagnostic imaging tests; blood tests; and metagenomics. Furthermore, the costs of the intervention will be estimated based on records of the time spent by exercise instructors, the use of sports facilities, and the purchase of exercise equipment. The time frame for the analysis will be approximately 6 months.

Two types of economic analysis will be conducted: an intention-to-treat and a per-protocol analysis. The intention-to-treat analysis will include all participants who will complete the trial, whereas the per-protocol analysis will include only those participants who will attend at least 70% of the exercise sessions.

To calculate the incremental cost-effectiveness ratio (ICER), we will examine the differences in costs and effectiveness between the intervention and control groups. Specifically, the incremental cost per participant will be divided by the incremental effectiveness to get the ICER. The ICER will be calculated for the incremental cost per person required to improve the health-related quality of life (HRQOL, assessed through Euroqol-5D [EQ-5D]) and functional capacity (assessed through Short Physical Performance Battery [SPPB]), and reduction of excess weight loss (%) and fat mass (%).

Finally, non-parametric bootstrap techniques of costs and health outcomes will be employed to estimate the probability that an exercise intervention would be cost-effective given a decision-maker’s willingness to pay for each additional unit of health outcome gained, or excess weight loss and fat mass reduced. Furthermore, cost-effectiveness acceptability curves will be presented, illustrating the probability of exercise intervention in this population could be cost-effective compared with the control group.

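### The 70% attendance rule can only filter the WBV arm, so neither per-protocol contrast (clinical or cost-effectiveness) is a randomised comparison, and no analysis is named as the basis for conclusions

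*Protocol article*

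**What the plan says.** Statistical methods defines the per-protocol set by attendance: "we will include only the participants who attend at least 70% of the sessions". It adds that these people must have been assessed both at baseline and after the intervention. Cost-effectiveness analysis uses the same threshold: "the per-protocol analysis will include only those participants who will attend at least 70% of the exercise sessions". Neither section says how the attendance condition applies to controls.

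Sessions belong to one arm. The section on training frequency, intensity and duration sets the schedule: "Those allocated to the WBV group will attend three weekly supervised sessions for 16 weeks, with a total of 47 sessions completed". Under Randomization, allocation, and blinding: "Both groups will receive standard care, but the intervention group will also engage in an exercise intervention as outlined below". No sham or attention sessions are described for controls.

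Both per-protocol analyses are nevertheless comparisons between arms. The clinical model is meant to "assess the interaction between group (control group vs. WBV) and time", and the incremental cost-effectiveness ratio (ICER) is built on differences between intervention and control.

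On purpose, Statistical methods says: "Per-protocol and intention-to-treat analyses will be performed in order to account for the possible dropouts during the study". The intention-to-treat set there is everyone with a baseline who goes on to "subsequently participate in at least one additional assessment following their group assignment". The economic section defines intention-to-treat differently, as those who complete the trial. Neither section names one of the two analyses as the basis for conclusions.

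**The concern.** Attendance is observed after randomisation and only in one arm. Restricting the WBV arm to good attenders leaves a selected group, and controls who would have attended poorly cannot be identified and removed to match. If those who keep coming would have changed more favourably anyway (better motivated, less pain, better recovery from surgery), that difference is credited to the training.

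The same filter enters the ICER. The Discussion says that positive cost-effectiveness results would lead the researchers to seek funding for a longer and larger study and to try to bring the programme into usual care of the national health system. An ICER based on selected attenders is a weak foundation for that step.

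**Working it through.** **Arm sizes.** The stated sample size reproduces. With partial eta squared 0.06, f² = 0.06/0.94. For the within-between interaction, λ = f²·N·4/(1 − 0.5), with df 3 and 3(N − 2). Power is 0.784 at N = 22 and 0.825 at N = 24. Adding 15% gives 24 × 1.15 = 27.6, hence 28, or 14 per arm. Only the 14 per arm is used below.

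**Threshold.** 16 × 3 − 1 = 47 sessions (two in week 1). 0.70 × 47 = 32.9, so 33 sessions.

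**Who is filtered, under the workable reading**

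| Condition | WBV | Control |
|---|---|---|
| At least 33 of 47 sessions | applies | cannot apply |
| Baseline and post-intervention assessments (Statistical methods) | applies | applies |

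The economic per-protocol rule states only the attendance condition.

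**Size under no treatment effect.** Two inputs are assumptions, because the article gives neither: the share p of the WBV arm that qualifies (80%, 70% or 50%, about 11, 10 or 7 of 14), and the correlation r between attendance propensity and change in the outcome (0 to 0.5). All 14 controls are assumed to be assessed.

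- False effect in SD units, with the top fraction p retained: r·φ(z)/p, where z = Φ⁻¹(1 − p). The factor φ(z)/p is 0.280/0.8 = 0.350, 0.348/0.7 = 0.497 and 0.399/0.5 = 0.798.
- Error rate: two-sided 5% t test of n against 14, with noncentrality (false effect)/√(1/n + 1/14) and n + 12 degrees of freedom. Example, n = 7 and r = 0.5: 0.399/√(1/7 + 1/14) = 0.862, critical value 2.093, error 13.0%.

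| r | 11 v 14 | 10 v 14 | 7 v 14 |
|---|---|---|---|
| 0 | 0; 5.0% | 0; 5.0% | 0; 5.0% |
| 0.1 | 0.04 SD; 5.1% | 0.05 SD; 5.2% | 0.08 SD; 5.3% |
| 0.3 | 0.10 SD; 5.7% | 0.15 SD; 6.4% | 0.24 SD; 7.8% |
| 0.5 | 0.17 SD; 7.0% | 0.25 SD; 8.9% | 0.40 SD; 13.0% |

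**Check by simulation** (20,000 trials per case, keeping the best attenders among 14). At r = 0.3 the bias is 0.10, 0.14 and 0.23 SD, with error 5.6%, 6.6% and 7.7%. At r = 0.5 it is 0.17, 0.23 and 0.38 SD, with error 7.4%, 8.2% and 12.3%. At r = 0 there is no bias and error is 5.0% to 5.1%.

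**Limit of the illustration.** It is a two-group comparison of change, whereas the plan tests a group-by-time interaction over four visits. A stable difference between attenders and others falls into the group main effect and does not bias the interaction. Only a link between attendance and change counts, which is why r is defined on change.

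**The case against.** - **Wording.** Taken literally, no control could qualify and the comparison could not be estimated. A reader might infer that the plan drops the control arm. The documents do not support that, since both sections describe a WBV-versus-control contrast. One sentence would limit the rule to WBV. That cures the ambiguity but not the one-sided selection.
- **Ordinary limitation.** Per-protocol sets in exercise-versus-usual-care trials commonly have this weakness, intention-to-treat is planned beside it, and ranking the two may sit in an unseen analysis plan. In part this stands: the randomised comparison is not replaced, and nothing says that the two results count as equal evidence. But the article does state the rule, twice, and the rule yields a selected contrast. That is not an omitted detail.
- **Purpose.** A reader might infer that the per-protocol set alone is offered as the answer to dropout. The sentence gives that purpose to both analyses jointly.
- **Controls.** A reader might infer that every control enters. In the clinical analysis, controls also need both assessments. What they lack is an attendance filter.
- **Size.** The correlation and the adherent share are not in the documents, and at r = 0.1 or below the distortion is negligible. This stands, so the result has to be given as a range that includes zero.
- **Remedy.** A complier estimate requires that allocation act only through sessions attended. WBV participants also get weekly trainer contact and monthly feedback on attendance, and outside exercise is unrestricted. At 14 per arm the estimate is essentially a rescaled intention-to-treat effect. This stands: it should be supportive, with the assumption stated.

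**Conclusion.** The point holds. As fixed in both sections, the per-protocol contrast filters one arm on attendance after randomisation and is not a randomised comparison. Neither section says which analysis carries the conclusion. In the economic section the problem is wider, because the intention-to-treat set there is itself a completer set, so neither economic analysis keeps everyone randomised.

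The false effect lies between 0 and about 0.4 SD, and the error rate between 5% and about 13%, for r from 0 to 0.5 and 50% to 80% adherent. The upper ends need both r = 0.5 and half the arm failing the threshold. These figures illustrate the possible size and do not predict it. The defect in the definition does not depend on them. The planned clinical intention-to-treat analysis limits the consequence, so this should be corrected but does not undermine the trial.

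**What to change.** 1. In Statistical methods and in Cost-effectiveness analysis, name intention-to-treat as the basis for conclusions.
2. In Cost-effectiveness analysis, define that set as all randomised participants, or match it to the definition in Statistical methods, instead of restricting it to those who complete the trial.
3. State in both places that the 70% rule (33 of 47 sessions) applies to the WBV arm only, say what qualifies a control, and label the analysis non-randomised and supportive.
4. Preferably replace or accompany it with a complier estimate that keeps both arms whole, for example two-stage least squares with randomised group as the instrument for sessions attended. State its exclusion assumption: allocation has no effect through trainer contact or outside exercise apart from the sessions. Label it supportive too.

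Cost: wording, with no new data, since attendance is already recorded at each session. The complier estimate will have a wider interval, and the sponsor gives up a per-protocol claim that may look more favourable.

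### As written, the four-visit repeated-measures ANOVA drops incomplete members of the plan's own intention-to-treat set, so the main result becomes a complete-case result

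*Protocol article*

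**What the plan says.** Three statements in the Statistical methods section of the protocol article bear on this point.

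- **Set.** The intention-to-treat analysis covers "all the participants who will undergo the baseline assessments and subsequently participate in at least one additional assessment following their group assignment". One follow-up visit is enough to belong.
- **Method.** For changes over time, "a repeated-measures ANOVA with Bonferroni correction will be used to assess the interaction between group (control group vs. WBV) and time", with the time factor given as "time (baseline vs. 2nd vs. 3rd vs. 4th assessments". Assumptions are checked as follows: "variance homogeneity and sphericity will be assessed with the Levene and Mauchly tests, respectively". Mauchly's test belongs to the classical ANOVA, not to a mixed model.
- **Dropout.** "Per-protocol and intention-to-treat analyses will be performed in order to account for the possible dropouts during the study". Nothing else is said about missing values. The per-protocol set is "only the participants who attend at least 70% of the sessions and undergo the baseline and post-intervention outcome assessments".

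The Cost-effectiveness analysis section uses the same term differently: "The intention-to-treat analysis will include all participants who will complete the trial".

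The Sample size section rests on the same four-visit test: "within-between interaction for two groups and four measurements was selected, assuming a correlation among the repeated measurements of 0.5". It allows for 15% attrition.

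**The concern.** A classical repeated-measures ANOVA needs a value at every level of the time factor for each participant. The stated set deliberately admits people who lack some of those values. The set and the method therefore do not fit together, and naming two analysis sets does not recover the people whom the method removes.

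The schedule makes this matter. Training lasts 16 weeks and falls between T2 (about 7 weeks after surgery) and T3 (about 24 weeks), so T3 is the first visit that shows the training effect. T4 comes at 18 months, with a long interval in which to lose people. Missing T4 alone removes a participant's T3 value from the main test. At stake is whether the superiority comparison for the four-visit outcomes, such as body composition and quality of life, describes the participants as randomised or only those who stayed for 18 months.

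**Working it through.** **1. The plan's own sample size.** Inputs from the Sample size section: two groups, m = 4 measurements, correlation 0.5, partial eta squared 0.06, alpha 5%, power 80%. Sphericity (epsilon = 1) is assumed, as it is not stated.

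- f² = 0.06 / 0.94 = 0.0638
- Noncentrality = f² × N × m / (1 − 0.5); df1 = 3; df2 = (N − 2) × 3
- At N = 24: noncentrality = 0.0638 × 24 × 4 / 0.5 = 12.26, df2 = 66, power 0.825
- At N = 22: power 0.784

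So 24 is the smallest even total above 80%, as the plan states. Then 24 × 1.15 = 27.6, rounded to 28.

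**2. What the method does with an incomplete participant.** Dummy data were made for 28 people, 4 of them missing only T4. A standard repeated-measures ANOVA routine rejected the data as unbalanced. Only the 24 complete cases (24 × 4 = 96 observations) could be used. A mixed model used all 28 people (28 × 4 − 4 = 108 observations). All 28 meet the stated intention-to-treat definition.

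**3. Power on complete cases.**

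| Scenario | Complete of 28 | Power |
|---|---|---|
| Planned 15% attrition | 28 × 0.85 = 23.8 | 0.805 (N = 23) to 0.825 (N = 24) |
| Assumed independent losses of 5% at T2, 5% at T3, 15% at T4 | 28 × 0.95 × 0.95 × 0.85 = 21.5 | 0.762 (N = 21) to 0.784 (N = 22) |

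In the second row 28 × 0.95 = 26.6 people have a T3 value, so about 5 T3 values are discarded. If the planned attrition all occurs at T4, about 4 are discarded.

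**4. Illustrative bias.** Assume that dropout before T4 occurs in one arm only and depends on the T3 value. Because baseline is a level of the time factor, the relevant quantity is the shift in the T1-to-T3 change. Listwise deletion removes the baselines of the same people, so the shift in the change equals the shift in the T3 mean × (1 − rho), where rho is the T1-T3 correlation.

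| Assumed dropout | Shift in T3 mean | Change, rho 0.7 | Change, rho 0.5 (plan) |
|---|---|---|---|
| 17% leave, odds about 2.7 times higher per SD worse | 0.149 SD | 0.149 × 0.3 = 0.045 | 0.149 × 0.5 = 0.074 |
| Worst 15% leave | 0.233 / 0.85 = 0.274 SD | 0.274 × 0.3 = 0.082 | 0.274 × 0.5 = 0.137 |

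Here 0.233 is the standard normal density at the 15th percentile. The shift in the change therefore runs from about 0.05 to 0.14 SD. It would flatter the training arm if its less successful participants were the ones who left.

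**The case against.** The strongest reply is that the article does not say incomplete cases are deleted. It is silent on missing values, and an analysis plan that is not shown could add imputation, which would reconcile the set with the ANOVA. This stands as a limit: a reader might infer that the set can never be analysed this way, and the documents do not support that. The reply does not remove the point, because the article fixes the set, the method and its means of accounting for dropout, and these do not work together.

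A reader might also infer that the trial is underpowered. The documents do not support this either: the sample was enlarged so that about 24 complete cases would remain, and the shortfall appears only with losses beyond the planned 15%.

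A reader might take the whole shift in the T3 mean (0.15 to 0.27 SD) as the bias. The planned test compares change from baseline, so much of that shift cancels.

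Someone seen only at T1 and T2 might look like a defect in the set's definition. The article does not make clear whether assignment precedes T2, and an analysis of all randomised participants would properly admit that person.

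The reach is also limited. The Wilcoxon and Mann-Whitney fallback can use the cases available for each comparison. Diet and microbiota are measured at three visits, so the four-visit rule does not apply to them.

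**Conclusion.** The inconsistency is real and is internal to the Statistical methods section. If nothing is imputed, the intention-to-treat result for the four-visit outcomes becomes a complete-case result. Under the planned attrition the cost in power is small, with power staying near 80%. The damage is that the label is untrue for the main test whenever visits are missed, that about 4 or 5 T3 values are thrown away in the scenarios above, and that selective dropout could bias the comparison. The figure of 0.05 to 0.14 SD for that bias is an illustration: it rests on outcome-related dropout in one arm and on a T1-T3 correlation of 0.5 to 0.7. The documents give no dropout mechanism. The second definition, in the Cost-effectiveness analysis section, adds a conflict that needs no assumption: one section admits participants with a single follow-up visit, the other only those who complete the trial.

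**What to change.** Replace the repeated-measures ANOVA with a linear mixed model for repeated measures that uses every observed visit of all randomised participants in their allocated arm. Treat visit as a category, include sex as a covariate (allocation takes sex into account), use small-sample degrees of freedom, and state group-by-visit contrasts at T3 and T4. Start from an unstructured covariance and name in advance the simpler structure to use if it does not converge. Make this the main analysis, with per-protocol supportive. Align the intention-to-treat definitions in the Statistical methods and Cost-effectiveness analysis sections. Stated multiple imputation would also resolve the conflict, but the mixed model is the simpler change.

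The cost is a few sentences and standard software, with no extra participants or visits. The one downside is that an unstructured covariance for four visits has 4 × 5 / 2 = 10 parameters to estimate from 28 people, hence the named fallback. The model relies on missingness depending only on observed data, which is weaker than what a complete-case analysis generally needs. The change should be made before any unblinded analysis.
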